**Version 1.0 16th July 2014**

### BACKGROUND AND RATIONALE

Oligofructose (OF) is a fructose-based oligosaccharide and defined in the EU as a dietary fibre. Enzymatically derived from the longer chain inulin, extracted from chicory, it is commonly used in processed food to improve mouth feel in fat-free products. OF is poorly digested and absorbed in the small bowel so passes to the colon where it is fermented by the bacteria usually resident in the colon, termed the microbiota. Its presence in the colon alters the composition of the microbiota, with reported potential benefits to health, leading to its description as a 'prebiotic'.

Recently, however, such poorly digested carbohydrates grouped together by the term FODMAP (fermentable oligo-, di-, mono-saccharides and polyols) have been proposed to exacerbate symptoms of irritable bowel syndrome (IBS) such as abdominal discomfort and bloating. Dietary exclusion of foods containing FODMAPs, such as wheat, dairy and certain fruit and vegetables, has been proposed as a treatment for IBS, with some evidence to support this. FODMAPs are thought to induce symptoms either by drawing water into the small bowel by osmosis, or through gaseous distension of the large bowel, or a combination of these combined with metabolite effects on motility.

The metabolic products of bacterial fermentation are short-chain fatty acids (SCFAs) and gases, such as hydrogen and methane. All of these can become substrates for growth of other bacteria, leading to a complex ecosystem. The SCFA butyrate provides nutrition to colonic epithelial cells, a phenomenon that has created interest in the role of butyrate, and the microbiota, in colon cancer, inflammatory bowel disease and functional gastrointestinal disorders. Recently butyrate has been shown to influence the development of colonic neurons, with potential effects on colonic motility and transit of luminal contents through the bowel. Thus, there appears to be a potential interaction between the colonic microbiota, complex carbohydrates in the diet and gastrointestinal transit with the suggestion of a possible effect on luminal serotonin levels. It is currently unclear how long a change in diet takes to alter the microbiota, but changes have been observed within a day of radical alteration in carbohydrate content of the diet.

Nottingham has world-leading expertise in Magnetic Resonance Imaging (MRI), particularly of in-body, non-invasive imaging of food transit and conformational change through the

gastrointestinal tract in humans. MRI imaging is also widely used to measure organ volumes. Within research conducted during studies of IBS patients (06GM006) and on the mode of action of Moviprep (10/H0906/50), the University of Nottingham has recently developed protocols to measure regional colonic volumes from coronal dual echo Fast Field imaging as briefly illustrated in the figure below. It is also possible to measure separately the volume of intraluminal gas (as it provides no signal) while the chyme usually gives a bright signal.

With MRC funding (NREC approval 11/EM/0245) the UoN GI MRI research group has also recently completed validation of a measure of whole gut transit time using MRI localisation of Gadolinium-filled capsules made of polyoxymethylene, a biologically inert substance

[figure not shown]

This panel shows (a) one coronal 'dual FFE' MRI image of the transverse colon of a healthy volunteer taken at fasted baseline. (b) a three-dimensional reconstruction of the different regions (ascending, transverse and descending) of the colon of another healthy volunteer.

Last year we combined these two techniques to gather pilot data on the effects of dietary OF and the longer chain polysaccharide from which it is derived, inulin, on colonic physiology. This pilot work found an 18% increase ( $p=0.02$ ) in fasting colonic volume after dietary supplementation with OF (abstract BSG 2014). This could not be accounted for by MRI measured changes in gas but breath hydrogen also rose significantly, suggesting increased levels of fermentation. One unifying hypothesis would be that increased nutrient availability leads to bacterial proliferation, increasing the mass of microbiota present. Whole gut transit time was slower, without reaching significance. This was the opposite of what we expected but is biologically plausible if delay in colonic transit maximises the opportunity for nutrient recovery.

The previous study was only a pilot study and as such had a few imperfections: it was uncontrolled with no open label and diet was not standardised between participants. We now wish to test our hypothesis that increased dietary content of poorly digested carbohydrates increases colonic volume in healthy volunteers. We will also test whether such changes can be explained by colonic gas volume measured, slowing of whole gut transit time or increased metabolic activity of the microbiota. We will also gather samples to allow exploratory work on how these dietary changes affect the urinary metabolome and, if future funding allows, changes in the microbiota.

# **TRIAL OBJECTIVES AND PURPOSE**

## **Purpose**

The purpose of the study is to investigate the effect of altering the amount of poorly digested carbohydrate in the diet for a week on the fasting colonic volume in healthy volunteers, and to explore possible mechanisms that underlie any differences found.

## **Primary Objective**

The primary objective is to determine the change from baseline in fasting colonic volume in healthy volunteers who follow a diet low in fermentable carbohydrates (the low FODMAP diet) to which carbohydrates are then added back as supplements, and to assess whether different carbohydrate supplements can alter the change measured.

## **Secondary Objectives**

Secondary objectives include:

- Examining factors that might explain changes in volume, including speed of whole gut transit time, colonic gas volume and degree of fermentation in the colon
- Exploring other effects of dietary change on the metabolic products of the microbiota

## **Hypotheses**

- The increase in fasting colonic volume measured by MRI will be greater in participants who supplement a low FODMAP diet with OF than in those who supplement with maltodextrin
- The Weighted Average Position Score of MRI transit markers 24 hours after ingestion will be no different between the two groups
- The increase in fasting colonic gas volume measured by MRI will be no different between the two groups
- Supplementation with OF will lead to a greater increase in fasting breath hydrogen than will supplementation with maltodextrin

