### **Secondary endpoints**

- Change in whole gut transit time (WGTT) as determined by Weighted Average Position Score (WAPS) of MRI transit markers 24 hours after ingestion, after one week of dietary intervention
- Percentage change in fasting colonic gas volume after one week of dietary intervention as measured by MRI
- Change in fasting breath hydrogen concentration after one week of dietary intervention, measured in parts per million
- Change in fasting breath methane concentration after one week of dietary intervention, measured in parts per million

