## Details of Trial Regimen

This study will use a parallel group design with 18 subjects per group.

### Visit 1 (Consent) – Day 0

Visit 1 will take place at the NDDC and last 20-30 minutes. After consent has been obtained participants will be screened against eligibility criteria will be enrolled if they are eligible. An MRI safety screening questionnaire will be completed as part of this process. A record will be taken of height, weight, current medication and any medical conditions and smoking history.

Participants will then fill in a food frequency questionnaire, the Comprehensive Nutrition Assessment Questionnaire (CNAQ), a questionnaire validated in an antipodean population to assess FODMAP content of the diet. This is pilot work to look at the utility of the CNAQ in a UK population.

Participants will then be instructed in how to complete a one week food diary. The first day of the food diary will be designated Day 1. They will also be told how to collect a stool sample.

They will be given to take away:

- A one week food diary based on the EPIC food diary, with guidance
- A stool collection kit including gloves, a cardboard tray and sample pots, with instructions

The stool collection kit has been used extensively in other departmental studies. A microbiology container that meets UN3373B standards for transport (Biobottle™; see picture) will be provided, along with a freezable gel pack. Participants will be asked to freeze the gel pack and collect 3 cherry-sized aliquots of stool from a single motion. This should be done at some point in the two days before Visit 2. Once collected, sample tubes can be put in the Bio-Bottle™ along with the gel pack and stored in the home freezer until visit 2.

[figure not shown]

Participants should not take excessive alcohol during the study and should abstain from alcohol from 8am on Day 6 (48 hours before the MRI scan).

### Visit 2 – Day 7

Visit 2 will take place in the NDDC and last around 90 minutes. Participants will attend around 8.30am, and will fast until they attend except for a small amount of water with essential tablets. They will return their stool samples, which will be immediately transferred to the -80C freezers of the NDDC. They will provide a urine sample which will be spun and frozen. Having emptied their bladders, participants will be asked to start a 24 hour urine collection.

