They will then be offered a standard breakfast with water and be asked to swallow 5 transit marker pills. The marker pills (see picture) are made of polyoxymethylene and are the shape of a size 1 gelatine capsule (20mm by 7mm). They are filled with 0.4 ml of 15µM Gadoteric acid solution and sealed with cyanoacrylate superglue. They have previously been used in studies with healthy volunteers and patients without complication (NRES approvals 10/H0906/50 and 11/EM/0245).

[figure not shown]

Note that up to 6 participants will attend visit 2 at the same time. 3 will take their marker pills between 8.30 and 9.30, and 3 will take them between 9.30 and 10.30 in accordance with the order of MRI scanning the following day.

During the visit participants will take part in a group session of advice on how to follow the low FODMAP diet. This will be led by [name], a registered dietitian trained in the instruction of the low FODMAP diet. Written material, published by Guy's and St Thomas' NHS Foundation trust, will be provided as it would be in clinical practice, on loan. This includes 2 booklets: "Reducing Fermentable Carbohydrates the low FODMAP way" and "Suitable Products for the low FODMAP diet". *Note that participants will not start to follow the low FODMAP diet until after their MRI scan the next morning.*

At the end of the visit participants will take away:

- A 24-hour urine collection bottle containing boric acid, with equipment to allow collection
- A standard packed lunch
- A standard meal for evening consumption

Participants may snack in addition to the meals provided but should use the food supplied for their main meals. They should continue their food diaries until the next morning. After 10pm that night no food should be eaten and only water should be drunk.

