### **Visit 4 – Day 14**

Visit 4 will take place at the NDDC and last 15 - 20 minutes. As for Visit 2, participants should fast until they attend around 8.30am. Stool and urine samples will be collected. Participants can return their low FODMAP advice booklets at this visit or Visit 5. The food diary should be continued until Visit 5.

Participants will be provided with a low FODMAP breakfast and asked to swallow 5 transit

markers. They should continue to take their supplement for the rest of the day. The last serving of supplement should be the second serving on Day 14.

At the end of the visit participants will take away:

- A 24-hour urine collection bottle containing boric acid, with equipment to allow collection
- A low FODMAP packed lunch
- A low FODMAP meal for evening consumption

Participants may snack in addition to the meals provided but should use the food supplied for their main meals. They should continue their food diaries until the next morning. After 10pm that night no food should be eaten and only water should be drunk.

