### **Assessment of Efficacy**

| Primary endpoint                         | Outcome Measure                                                    |
|-------------------------------------------------|---------------------------------------------------------------------------|
| Percentage change in fasting colonic volume     | Difference in mean response between arms                                  |
| Secondary endpoints                      | Outcome Measure                                                    |
| Change in whole gut transit time                | Difference between treatment arms by ranking, unless normally distributed |
| Percentage change in fasting colonic gas volume | Difference in mean response between arms                                  |
| Change in fasting breath hydrogen               | Difference in mean response between arms                                  |
| Change in fasting breath methane                | Difference in mean response between arms                                  |

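### The transit hypothesis is worded on the 24-hour WAPS itself while the endpoint and analysis table use the change, and the unadjusted change comparison wastes the Day 8 score

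*Protocol*

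**What the plan says.** In the Protocol, the second item under Hypotheses says that the WAPS "of MRI transit markers 24 hours after ingestion will be no different between the two groups". No baseline, change or visit is mentioned. The other three hypotheses in that list are all framed as increases; the gas item, for example, reads "The increase in fasting colonic gas volume measured by MRI will be no different between the two groups".

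Under Secondary endpoints, the transit endpoint is "Change in whole gut transit time (WGTT) as determined by Weighted Average Position Score (WAPS) of MRI transit markers 24 hours after ingestion", assessed after the week of intervention. The Assessment of Efficacy table lists "Change in whole gut transit time" and gives the comparison as "Difference between treatment arms by ranking, unless normally distributed". The table does not name the WAPS; the link comes from the endpoint list.

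The score is obtained twice. At Visit 2 (Day 7) participants will "be asked to swallow 5 transit marker pills", and these are located on the Day 8 scan before the first supplement serving. At Visit 4 (Day 14) the Protocol says "Participants will be provided with a low FODMAP breakfast and asked to swallow 5 transit" markers, which are located on the Day 15 scan. On size, Details of Trial Regimen says "This study will use a parallel group design with 18 subjects per group".

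**The concern.** There are two linked points.

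First, the hypothesis and the endpoint do not name the same variable. Every completer will have a score at both scans, so both a between-group comparison of the score and one of the change can be computed. With small arms the two can differ on statistical significance, because a chance baseline difference affects them differently and their precision differs. Transit is one of the mechanisms the Protocol offers to explain a volume change, so the variable being tested should be unambiguous.

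Second, the variable that the endpoint list and the table agree on, the change, is compared with no use of the Day 8 score beyond subtraction. Subtraction adds the Day 8 measurement noise to the Day 15 noise. If the two scans are only weakly correlated, this costs more than it gains. The hypothesis is one of no difference, and readers tend to take a non-significant result as support for such a hypothesis, so lost precision matters here.

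**Working it through.** **Which passages agree**

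| Place in the Protocol | Variable |
|---|---|
| Hypotheses, item 2 | 24-hour WAPS, visit not named |
| Secondary endpoints, item 1 | change in transit, by 24-hour WAPS |
| Assessment of Efficacy, transit row | change in transit |

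Two of the three agree, and they are the two that define the endpoint and its analysis. The hypothesis is the one out of line.

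**Inputs.** There are 18 per arm (Details of Trial Regimen). The Protocol gives no SD, effect size, power or between-scan correlation for the WAPS; its sample-size figures concern colonic volume only, so there is no stated figure to reproduce. Assumptions: equal SD (σ) at both scans; correlation ρ of 0.2, 0.5 or 0.8; true difference of 0 or 0.8σ; two-sided 5% tests; normal scores.

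**Standard error of the arm difference.** Each is the residual SD times √(2/18) = 1/3. The residual variances are:
- Day 15 score alone: σ²
- unadjusted change: 2σ²(1−ρ)
- Day 15 score with the Day 8 score as covariate: σ²(1−ρ²), ignoring the small cost of estimating the slope

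| ρ | Score alone | Change | Adjusted | Change ÷ score alone, √(2(1−ρ)) | Adjusted ÷ change, √((1+ρ)/2) |
|---|---|---|---|---|---|
| 0.2 | 0.333σ | 0.422σ | 0.327σ | 1.26 | 0.77 |
| 0.5 | 0.333σ | 0.333σ | 0.289σ | 1.00 | 0.87 |
| 0.8 | 0.333σ | 0.211σ | 0.200σ | 0.63 | 0.95 |

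The change is less precise than the score alone whenever 2(1−ρ) exceeds 1, that is, when ρ is below 0.5. The adjusted comparison is at least as precise as either, because (1+ρ)/2 and 1−ρ² never exceed 1 for ρ between 0 and 1.

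**Power by simulation, true difference 0.8σ**

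| ρ | Change, t-test | Adjusted | Change, rank test | Adjusted, ranked scores |
|---|---|---|---|---|
| 0.2 | 45% | 65% | 42% | 63% |
| 0.5 | 65% | 76% | 62% | 72% |
| 0.8 | 96% | 97% | 95% | 94% |

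The t-test on the Day 15 score alone has about 64% power throughout.

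**Disagreement between score alone and change.** With no true difference, the two disagree on significance in about 7–9% of trials. If each is tested at 5%, the chance that at least one is positive is 0.05 plus half the discordance. With discordance of 7.4% to 9.0%, that is 8.7% to 9.5%. With a true 0.8σ difference, t-test discordance is 32–36%.

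**Does the covariate remove the ambiguity?** On the score scale it does: with the Day 8 score in the model, using the change instead of the Day 15 score only shifts the slope on the Day 8 score by 1, and the arm difference is the same. On ranks it does not, because the rank of a difference is not the difference of ranks. A single outcome must therefore be named.

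**The case against.** The strongest reply is that the endpoint is not defined in two competing ways. The section that defines endpoints and the table that fixes the analysis both say change, so an analyst following them reaches one variable; a loosely worded hypothesis does not override them. That stands, and it is why the first part of this point is a wording correction.

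A reader might infer something stronger: that the two definitions can give opposite verdicts on transit. The documents do not support this. Under randomisation both comparisons have the same expected arm difference. What can differ is whether a p-value falls below 0.05. The 32–36% figure also depends on an assumed 0.8 SD effect that the Protocol nowhere gives; under the Protocol's own hypothesis of no difference, the figure is 7–9%.

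A reader might also infer that the analyst is free to choose the definition after seeing both results. The agreement between endpoint list and table argues against that. Blinding of analysts until the secondary analyses are complete limits choice by which supplement is favoured, although it does not hide p-values.

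Two further objections have some force. Covariate adjustment could be left to a statistical analysis plan, but this Protocol already specifies the comparison in its table, so improving that line is fair. And the simulation uses continuous normal scores, whereas the WAPS summarises five pills over eight bowel sections; the power figures are therefore indicative.

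**Conclusion.** The mismatch is real but narrow: one hypothesis sentence is out of line with an endpoint list and analysis table that agree. Separately, the unadjusted change comparison is an inefficient use of data already being collected. Under the stated assumptions, adjustment raises t-test power by about 20 percentage points at ρ = 0.2, 11 at 0.5 and 1 at 0.8. On ranks the gain is about 21 and 10 points at the two lower correlations, and the methods are about equal at 0.8 (95% against 94%).

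The endpoint is secondary. Nothing here touches the primary endpoint, the sample size or data collection. The size of the gain depends on a correlation and an effect that the documents do not give. That adjustment is no less precise than the unadjusted change holds on the score scale across the assumed range, apart from the degree of freedom spent.

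**What to change.** 1. In Hypotheses, reword the second item so that it refers to the change in 24-hour WAPS from the Day 8 scan to the Day 15 scan, in line with Secondary endpoints and Assessment of Efficacy.
2. In the transit row of Assessment of Efficacy, state one analysis: compare arms on the Day 15 WAPS with the Day 8 WAPS as covariate or, if the scores are not normally distributed, fit the same model to the ranked scores. Name the Day 15 WAPS as the single outcome in both cases. On the score scale this estimates the same arm difference as an adjusted analysis of the change; on ranks it does not, so the outcome must be fixed in advance.

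The cost is one reworded sentence, one table line and one degree of freedom. No new data, visits or participants are needed.

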## **STATISTICS**

### **Sample Size and justification**

We will recruit up to 45 participants in order to gather 36 complete data sets.

Our pilot data found an 18% increase in colonic volume after normal diet was supplemented with OF. The null hypothesis would be that there is no change in colonic volume in either arm of the planned study (OF or maltodextrin). The effect of the low FODMAP diet is uncertain but should be the same in both arms. If our hypothesis is correct then volume may decrease in the maltodextrin arm.

Data from a previous 4-period crossover study of healthy volunteers found a within-individual coefficient of variation for fasting colonic volume of 17% (unpublished). A sample size of 36, randomised 1:1, would give 80% power to detect a 15% increase in the change in volume between treatment arms ( $\alpha = 0.05$ , 1-tailed). Given our pilot work and the resulting study hypothesis we feel that a 1-tailed test is appropriate. Given the mechanistic nature of the study withdrawals and dropouts will be replaced.

Data will be assessed for normality using the Shapiro-Wilk test and other such methods as appropriate. Where normally distributed, endpoints will be assessed using parametric methods. The primary outcome measure will be analysed by t-test to compare the primary

endpoint between groups. Where the data is not normally distributed, non-parametric methods will be used.

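### Two hypotheses predict no difference in transit and gas volume, but the plan only compares arms for a difference with 18 per arm, so only a non-significant result could support them

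*Protocol*

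**What the plan says.** The Protocol's Hypotheses section has four items. Two are directional: oligofructose is expected to raise colonic volume and breath hydrogen more than maltodextrin. The other two predict no effect. For gas: "The increase in fasting colonic gas volume measured by MRI will be no different between the two groups". For transit, the Weighted Average Position Score "of MRI transit markers 24 hours after ingestion will be no different between the two groups".

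The table under Assessment of Efficacy gives the comparison for each endpoint. For gas it reads "Percentage change in fasting colonic gas volume | Difference in mean response between arms". For transit it reads "Difference between treatment arms by ranking, unless normally distributed". Sample Size and justification adds only that methods will be parametric or non-parametric according to normality, and it names a t-test for the primary outcome.

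The trial's size comes from the primary endpoint: "A sample size of 36, randomised 1:1, would give 80% power to detect a 15% increase in the change in volume between treatment arms". The variability behind it is also for colonic volume; an earlier crossover study "found a within-individual coefficient of variation for fasting colonic volume of 17% (unpublished"). No SD is given for gas volume or WAPS.

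Gas and transit are there to interpret the primary result. The Background and the Secondary Objectives both list them among the factors that might account for a change in volume. Of transit in the pilot, the Background says: "Whole gut transit time was slower, without reaching significance". It adds that slowing would be biologically plausible.

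**The concern.** A hypothesis of no difference cannot be supported by failing to find a difference. It needs an interval narrow enough to exclude differences that would matter, and so a statement of what would matter. Here the hypotheses and the stated comparisons do not fit each other. The two directional hypotheses can be supported by a significant result. The two null ones can be supported only by a non-significant one, and the smaller or noisier the trial, the more often that occurs.

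What is at stake is the mechanistic reading. If oligofructose raises colonic volume, the next question is whether gas or slower transit accounts for it. Under the present wording, imprecision on those two endpoints counts towards setting them aside. Because the pilot's transit result leaned towards slowing, a real transit difference cannot be dismissed in advance.

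**Working it through.** **1. The plan's own sample size.** Inputs from Sample Size and justification: difference 15%, variability 17%, one-sided 5%, power 80%, 36 in total. Formula: n per arm = 2 × SD² × (z₀.₉₅ + z₀.₈₀)² / difference², with (1.645 + 0.842)² = 6.18.

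- Raw scale, 17% taken as the SD of the change: 2 × 289 × 6.18 / 225 = 15.9, so 16 per arm (17 with the t distribution).
- Log scale, difference ln 1.15 = 0.140 and SD √ln(1 + 0.17²) = 0.169: 18.04, so 19 per arm. Power at 18 per arm is 79.9% (normal) or 78.5% (t).

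The stated 36 is therefore reproduced to within about two participants, and it concerns colonic volume only. Nothing in it bears on gas or WAPS.

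**2. What 18 per arm can detect on gas or transit.** The 18 per arm is stated under Details of Trial Regimen ("This study will use a parallel group design with 18 subjects per group"). With no SD for either endpoint, the between-arm difference in change is expressed in SD units of that change. The standard error is √(2/18) = 0.333 SD on 34 degrees of freedom. Power is from the noncentral t with noncentrality d/0.333.

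| True difference | Noncentrality | Missed, two-sided 5% | Missed, one-sided 5%, correct direction |
|---|---|---|---|
| 0.5 SD | 1.5 | 69% (power 0.308) | 57% |
| 0.8 SD | 2.4 | 35.5% (power 0.645) | 24% |

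Power reaches 80% at 0.96 SD two-sided, or 0.85 SD one-sided.

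**3. Width of the interval.** 95% half-width: t(0.975, 34) × 0.333 = 2.032 × 0.333 = 0.68 SD. 90% half-width: 1.691 × 0.333 = 0.56 SD. Even an observed difference of exactly zero would typically leave differences of up to two-thirds of an SD open.

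**4. What it would take to show no relevant difference.** The Protocol states no margin, so a range is shown. The method is two one-sided 5% tests (a 90% interval inside ± margin) with a true difference of zero. Power at 18 per arm was simulated. n per arm = 2 × ((1.645 + 1.282) / margin)².

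| Margin | Power at 18 per arm | n per arm for 80% |
|---|---|---|
| 0.5 SD | 2% | 69 |
| 0.6 SD | 13% | 48 |
| 0.8 SD | 52% | 27 |
| 1.0 SD | 80% | 18 |

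Requiring the 95% interval to lie inside the margin is stricter. At a margin of 1.0 SD the estimate must fall within 1 − 0.68 = 0.32 SD of zero. That is 0.32 / 0.333 = 0.97 standard errors, which happens about two-thirds of the time.

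**5. Limits of these figures.** The two-sided 5% level is an assumption. The only sidedness in the Protocol is one-tailed, and it is argued from the directional primary hypothesis. The t-based figures are only a guide for WAPS, which is ranked unless normally distributed. Whether 0.5 or 0.8 SD matters physiologically cannot be judged from the Protocol.

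**The case against.** The strongest reply has four parts.

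*The Protocol never says how a non-significant result will be interpreted.* This is correct. A reader might infer that non-significance will be reported as proof of no effect, but no section says so. The pilot transit result points the other way: it was non-significant, yet it was reported as slower and discussed as plausible. The Background does say that gas could not account for the pilot's volume increase, but not how that was judged. What stands against the plan is narrower: it offers no other result by which these two hypotheses could be supported.

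*The explanation of the volume change is an open question.* This is also fair. The Background and Secondary Objectives ask whether gas or transit might explain the change; they do not assert that neither does. But the Hypotheses section gives the expected answer for both, and that answer is the part that cannot be supported.

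*The table names outcome measures, not tests, and margins or interval rules often sit in a statistical analysis plan.* A difference in means can indeed be reported with a confidence interval, and an unseen analysis plan may add a criterion. The absence of a margin is therefore not the fault by itself. The fault is that hypotheses and comparisons are both fixed in the Protocol and do not match.

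*The trial is not bound to confirm these hypotheses whatever the truth.* A reader might infer that from the miss rates, but power is 80% at 0.96 SD, so a large difference would probably be found. Nor can the pilot say how large a transit effect to expect: it was uncontrolled, without standardised diet, and no transit effect size is reported.

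**Conclusion.** The point holds as a mismatch between two stated hypotheses and the comparisons planned for them. With 18 per arm, a non-significant result on gas or WAPS would be compatible with moderate and fairly large differences. Given the assumptions listed in the working, exclusion is realistic only for margins of around 1 SD or wider. The one-sided figures are milder but lead to the same conclusion.

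It does not show that the sponsor intends to treat non-significance as proof. Both endpoints are secondary and the primary comparison is untouched; what is affected is how far the trial can speak to mechanism. The point is worth correcting because the change is one of wording.

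**What to change.** Reword both hypotheses as estimation aims: the between-arm difference in the change in WAPS, and in gas volume, will be estimated and reported with a 95% confidence interval. This is compatible with the outcome measures already tabulated; if WAPS is analysed by ranks, an interval for a location shift serves the same purpose.

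Add one sentence saying that a non-significant result will not be taken as showing no difference, or as ruling out gas or transit as an explanation of the volume change.

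If a conclusion that gas or transit does not explain the change is wanted, allow it only when the interval excludes a margin fixed before unblinding. That margin must not be derived from the volume difference the trial observes. The gas endpoint is a percentage change, which cannot be set directly against a change in colonic volume, so add the absolute change in gas volume in mL.

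The cost is two reworded hypotheses, one reporting sentence and one additional summary from scans already planned. No further participants or visits are needed and the primary analysis stays as it is. The price is a more cautious mechanistic conclusion, because 18 per arm can exclude only large differences.
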